### Eligibility criteria

The inclusion criteria are: (1) aged 18 years and above; (2) postinjury <6 months; (3) cervical or thoracic incomplete SCI; (4) able to sit without support for 30 s and (5) sufficient upper-limb function to voluntarily perform arm cycling movement on a stationary arm bike, with or without use of gripping aids.

The exclusion criteria are: (1) ongoing issues with shoulder instability or shoulder pain; (2) contraindications to exercise in an upright posture (eg, postural hypotension, unresolved pressure ulcer, uncontrolled cardiovascular conditions); (3) pregnancy and (4) unable to understand explanation of the study and/or instructions of the intervention.

### Interventions

All participants will receive standard in-patient rehabilitation care at the spinal unit. The ACET group will additionally undertake 8 weeks of progressive, unsupervised ACET with a stationary arm bike (MagneTrainer ER).


### Assessments

The study has four assessment periods—baseline (T0), 4 weeks (T1), postintervention (T2), and 6 months follow-up (T3). Assessments from T0 to T2 are expected to occur while participants are still within 12 months postinjury. However, the T3 assessment may occur during the chronic phase of SCI for some participants. We expect that all participants will have the baseline and 4 weeks assessments conducted at the spinal units. We also anticipate some participants will have the postintervention and 6 months follow-up assessments at the spinal units or at the University of Birmingham, whichever is more convenient to them.

### Randomisation

All participants will undergo one baseline assessment and one 4-week assessment to estimate individuals’ spontaneous recovery rate. After the 4-week assessment, participants will be randomly allocated (1:1) to an ACET group or a standard care control group using a minimisation randomisation^41^ to balance covariates of level of injury and classification of injury between groups. The procedure will start from the first participant being allocated to a study group at random. For each subsequent participant, we determine which study group would lead to better balance between the groups in the variables of interest. The randomisation will be performed by [name] who will not be involved in recruitment of participants. However, it is not achievable in this study to blind participants or researchers conducting the assessments given the type of the intervention and resources available. Figure 1 illustrates the trial flow chart.

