## Methods and analysis

### Study design

This study is a multicentre, two parallel-group, non-blinded, randomised controlled trial of a self-directed ACET in individuals with subacute SCI (<6 months postinjury). The study was approved by the North of Scotland Research Ethics Committee (1) (22/NS/0054) and prospectively registered on the International Standard Randomised Controlled Trial Number registry (ISRCTN17247972). This research is the second part of a larger trial which consists of a feasibility study (ISRCTN89333770; completed) and a randomised control trial (this study). The study will be conducted in accordance with the Declaration of Helsinki. The study protocol is reported following the SPIRIT checklist (online supplemental appendix 1).

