### Recruitment and consent process

Recruitment will be conducted at the Princess Royal Spinal Cord Injuries Centre (PRSCIC) and at the Yorkshire Regional Spinal Injuries Centre (YRSIC). Recruitment will be carried out by the medical team of the spinal units. Patients who meet the eligibility criteria will be approached by a member of the medical team and given a copy of the participant information sheet to read. They will be given at least 24 hours to consider their participation to the study. Prior to the consent process, potential participants will be given the opportunity to ask the research team questions regarding the study. The research team will obtain written informed consent from all participants prior to any data collection.

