### Statistical analyses

Statistical analyses will be performed using the latest version of SPSS available at the time of analysis (IBM, Armonk, NY, USA). The distribution of the continuous variables will be tested for normality using the Shapiro-Wilk test and appropriate descriptive parameters will be reported and statistical tests will be applied accordingly. A mixed-model two-way repeated measures ANOVA, with group as the between-participant factor and time as the within-participant factor, will be used to compare outcome measures. This analysis will be performed according to the intention to treat approach. Post hoc tests will be applied where there is a main effect. Significance level will be set at 0.05 for all statistical tests. For the data that are normally distributed, effect sizes of partial eta squared (η2p) or Cohen’s d will be calculated. Additionally, potential confounders (eg, age, days since injury) will be included in the analysis. Subgroup analyses (eg, based on AIS classification) will also be performed if appropriate.

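### As described, allocation after the first participant has no random element and does not balance centre in an open-label trial, and the balanced factors are not named in the analysis model

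*Protocol article*

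**What the plan says.** The Randomisation section of the protocol article states that "participants will be randomly allocated (1:1) to an ACET group or a standard care control group" by minimisation, after the 4-week assessment, "to balance covariates of level of injury and classification of injury between groups". It then describes the steps: "The procedure will start from the first participant being allocated to a study group at random", and after that, "For each subsequent participant, we determine which study group would lead to better balance between the groups in the variables of interest". It gives no probability of following the balancing arm and no rule for ties. Centre is not a factor, although the Recruitment and consent process section names two spinal units.

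Study design describes a "multicentre, two parallel-group, non-blinded, randomised controlled trial", and the Randomisation section adds that "it is not achievable in this study to blind participants or researchers conducting the assessments". The person who allocates takes no part in recruitment.

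The Statistical analyses section plans a group-by-time repeated measures ANOVA and says that "potential confounders (eg, age, days since injury) will be included in the analysis". Injury level, injury classification and centre are not named as model terms. AIS grade appears there only as an example of a possible subgroup analysis.

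Table 1 puts the allocation column before T1 and lists T1 in the period after allocation, whereas the Randomisation text allocates after the 4-week (T1) assessment.

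**The concern.** A balancing rule with no random element can be worked out by anyone who knows the earlier allocations and the next patient's injury level and classification. When assessors are unblinded, concealment of the coming allocation is one of the few protections left. The research team obtains consent, and its researchers hold the pre-intervention conversation and supervise the first exercise session, so some members can know allocations at both units. Someone who foresees the arm could, without intending to, influence the T1 measurements or the injury grading, which is itself an input to the rule. T1 matters because it is used to estimate each participant's spontaneous recovery.

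Two further points follow from the same section. Standard rehabilitation is the control condition and is delivered by two units, yet nothing keeps the arms balanced within a unit. And if the allocation forces balance on prognostic factors that the model then leaves out, the standard error is too large for any comparison those factors predict.

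**Working it through.** **1. The plan's own figure.** Inputs from Study population and sample size: d = 0.85, 80% power, 5% level, independent t-test. The normal approximation gives 2 × (1.960 + 0.842)² / 0.85² = 15.70 / 0.7225 = 21.7, so 22 per arm. The exact noncentral t gives 22.73, so 23 per arm, with 80.5% power. The stated 46 reproduces and is not in dispute here.

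**2. Predictability at the moment of allocation.** The article gives no factor levels or prevalences, so these are assumed: two injury levels at 50/50; classification in two levels (50/50) or three (20/30/50); two equal centres; 60 participants; minimisation on marginal totals; ties broken by a coin; 1,500 simulated sequences per setting. If F is the share of allocations after the first that are not ties, and p is the probability of following the balancing arm, a fully informed observer guesses correctly in F × p + (1 − F) / 2 of cases.

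| Rule | F | Correct guesses |
|---|---|---|
| p = 1, no centre (as described) | 0.716 to 0.728 | 0.858 to 0.864 |
| p = 1, centre added | 0.796 to 0.801 | 0.898 to 0.900 |
| p = 0.8, no centre | 0.794 to 0.803 | 0.738 |
| p = 0.8, centre added | 0.859 to 0.861 | 0.757 to 0.758 |
| p = 0.7, centre added | 0.889 to 0.891 | 0.677 to 0.678 |

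For the first row: 0.716 + 0.284 / 2 = 0.858. For the fourth: 0.859 × 0.8 + 0.141 / 2 = 0.758. Separate runs of the same model gave about 70% forced and 85% guessed.

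**3. How far that knowledge reaches.** Applying the rule to one centre's tally alone gives about 57% correct. A guess from a complete tally that is 1, 2, 3 or 5 allocations out of date is right 67%, 61%, 57% or 54% of the time. Consent comes at least four weeks before allocation, so a guess at consent is usually of this stale kind.

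**4. Balance within centre.** As described, the larger of the two within-centre arm differences averages 3.2, with a 95th percentile of 7 to 8. It is 6 or more in about 18% of simulated trials. With centre added and p = 0.8, the mean is 1.5, the 95th percentile 3, and a difference of 6 or more occurs in under 1%.

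**5. Leaving the balanced factors out.** Let the factors explain a share R² of the variance of the analysed quantity (assumed). With near-perfect balance, the difference in means has variance proportional to 1 − R², but the unadjusted t-test estimates it as if proportional to 1. The approximate size is P(|Z| > 1.96 / √(1 − R²)):

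- R² = 0.2: 1.96 / 0.894 = 2.19, size about 2.8%.
- R² = 0.4: 1.96 / 0.775 = 2.53, size about 1.1%.

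Simulation (46 participants, three classification levels, 4,000 trials) agrees:

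| R² | Size, unadjusted | Size, adjusted | Power, unadjusted | Power, adjusted |
|---|---|---|---|---|
| 0.2 | 3.1% | 4.9% | 83% | 88% |
| 0.4 | 1.2% | 4.6% | 86% | 95% |

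**6. The same question for a change contrast.** When the factors shift a participant's level equally at every visit, they cancel from the change, which with two time points is the group-by-time test. Simulated size was then 5.5% and 5.2% at R² 0.2 and 0.4 (3,000 trials; Monte Carlo standard error √(0.05 × 0.95 / 3000) = 0.4 points). There is no conservatism in that case.

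**The case against.** Four points can fairly be made on the other side.

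- **Calling the rule deterministic is a reading of a condensed article.** The same section calls the allocation random and cites a method paper, and ties (about 28% of allocations in simulation) need some rule. A full protocol could hold a random element. This stands as a limit. But the article sets the procedure out step by step and places chance only at the first step, so the description needs correcting or completing.
- **Predictability can be overstated.** A reader might infer that staff at either unit can foresee allocations, or that patients can be selected before consent. The documents do not support either. The 85% needs the full two-centre tally at the moment of allocation; the allocator does not recruit; and consent, baseline and the 4-week assessment come first. The 57% is not a ceiling either, since a researcher working at both sites could know more.
- **The covariate list is open.** It gives examples and excludes nothing, and the final list is often left to an analysis plan. A reader might also infer that the planned ANOVA is conservative throughout; step 6 shows that it is not. The loss arises for a comparison of levels, for the group main effect, or where the factors predict recovery over time. The last is plausible in subacute injury but is not shown in the documents.
- **Centre with two sites and 60 participants is partly a design preference.** No difference in rehabilitation between the units is documented, and the type and duration of standard care are recorded. This lowers the weight of the point; it does not make balance by centre costly.

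**Conclusion.** The point holds in a bounded form. The described procedure has no stated random element after the first participant, does not balance centre, and is used in an open-label trial. Someone with both units' allocations could predict about 85% of assignments as they are made; this rests on assumed factor prevalences and equal centres. The main risk is biased T1 measurement or injury grading just before allocation, not selection at approach.

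The modelling part is conditional. If the balanced factors explain 20% to 40% of the variance of the analysed contrast (assumed), omitting them gives a true size of about 1% to 3% and costs about 5 to 10 points of power. If they shift only the level equally at all visits, the group-by-time test is unaffected. In neither case is the false-positive rate inflated.

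The conflict between the Randomisation text and Table 1 matters here: whether T1 comes before or after allocation decides whether an assessor at T1 might foresee the arm or already knows it.

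**What to change.** 1. State that each participant goes to the better-balancing arm with a probability below 1, for example 0.8, and 50:50 on ties.
2. Add centre as a minimisation factor only together with step 1. Centre alone raises predictability to about 89% to 90%; the two together bring it to about 75%.
3. Name injury level, AIS grade and centre as fixed terms in the between-group models, with their interactions with time, so that they also help where they predict recovery.
4. Reconcile the Randomisation text and Table 1 on the order of allocation and T1.

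The cost is a short amendment to the allocation procedure and a few words in the analysis section. Overall balance becomes slightly looser (mean arm-size difference about 1.1 instead of 0.45 in simulation), and the extra terms use a few degrees of freedom. If recruitment has begun, the allocation change can help only later participants, but the covariate change still applies in full.

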**Trial registration number:**

ISRCTN17247972

STRENGTHS AND LIMITATIONS OF THIS STUDYThis multicentre, randomised controlled trial will evaluate trunk control over time in individuals with spinal cord injury (SCI) following a self-directed exercise programme, compared with those receiving standard care.The study assesses the broader impact of the intervention on individuals’ health and functioning, including impairments, activities, participation and environmental and personal factors.The study will use both quantitative and qualitative methods to enable multidimensional evaluation of patients’ responses to the intervention.A limitation is that neither the participants nor assessors are blinded to group allocation, which may introduce bias to the results.

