#### Primary outcome measure

The primary outcome of the study is trunk control, assessed by:

*1. Volitional control of the trunk*

*Static and dynamic sitting balance*. Sitting balance will be assessed using the following tasks: unsupported sitting for 30 s, forward and lateral reaching,^12 43^ bilateral voluntary arm raise^44^ and rapid shoulder flexion.^12^ Participants will perform each task five times while seated on a plinth with their trunk unsupported, feet flat on the floor, hips and knees positioned at 90°, and the popliteal fossa approximately a palm’s width away from the edge of the plinth.

For the unsupported sitting task, participants will be instructed to sit unsupported as stable and upright as possible for 30 s (figure 2A). For the multidirectional reaching tasks (figure 2B and C), participants will be asked to sit in an upright position and use the less affected arm to reach forward and to the side as far as possible without losing balance. For the voluntary arm raise task (figure 2D), participants will be instructed to hold a resistance band with both hands and move the band up by flexing the shoulder joints to the maximum active range of motion. A rapid shoulder flexion task will be used to assess anticipatory and compensatory postural adjustments, whereby participants will, while sitting, raise their arms to a horizontal outstretched position as quickly as possible in response to a short, sharp verbal cue (figure 2E). Movement of the upper limbs and trunk will be captured in 2D videos recorded with a camera in 1080 p at 30 frames per second (iPad mini fifth generation, Apple, CA, USA). The camera will be placed at the angle perpendicular to the movement plane. Furthermore, the kinematics of the trunk will be recorded at 100 Hz using an inertial measurement unit (IMU)^45^; (Sessantaquattro+, OT Bioelettronica, Turin, Italy) placed at the fourth thoracic spinous process (figure 3). Sitting posture (spinal curvature at rest),^46^ reaching distance,^12^ angular displacement of the trunk^47^ and range of motion of the shoulder joints^44^ will be analysed from the 2D videos.

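### The reason given for open assessment covers the live session only, and no masking is stated for the later video extraction of the key primary kinematics

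*Protocol article*

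**What the plan says.** The Study design section labels the trial non-blinded. The Randomisation section gives the reason: "it is not achievable in this study to blind participants or researchers conducting the assessments given the type of the intervention and resources available". The strengths and limitations box repeats that "neither the participants nor assessors are blinded to group allocation" and accepts that this may bias the results.

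Under Primary outcome measure, trunk control is assessed through sitting-balance tasks and neurophysiological measures. For the tasks, "Movement of the upper limbs and trunk will be captured in 2D videos recorded with a camera", and four quantities (sitting posture, reach distance, trunk angular displacement and shoulder range) "will be analysed from the 2D videos". In parallel, "the kinematics of the trunk will be recorded at 100 Hz using an inertial measurement unit". High-density EMG and evoked potentials are also recorded as signals.

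Study population and sample size bases the trial on trunk angular displacement in forward reaching, with Cohen's d = 0.85.

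The article does not say who reads the videos, whether files are coded, or whether the reader knows the group or the visit.

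**The concern.** The justification and the measurement step do not match. It is plausible that someone running a session on the ward cannot be kept unaware of allocation. But the session yields a recording, and the outcome value arises later when that recording is analysed. Arm cycling is not one of the filmed tasks, so the type of intervention is no obstacle to masking at that later stage.

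If video extraction involves any judgement, for example in choosing a frame or placing a landmark, a reader who knows both arm and visit can move the value in the expected direction. The exposed quantities include the one on which the trial is sized. The ACET intervention section also shows that researchers hold the adherence conversation and supervise the first exercise session, so at least some of the team know who is in the exercise arm. The article names no reader separate from them.

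**Working it through.** **1. The stated reason against each step**

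| Step | What the article states | Does the stated reason cover it? |
|---|---|---|
| Participant performs the task | Unblinded | Yes |
| Researcher conducts the session | Unblinded | Yes |
| Posture, reach, trunk angle and shoulder range are taken from stored video | Done from recordings; reader and masking not stated | No |
| IMU and EMG signals are processed | Instrument-recorded; masking not stated | No |

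The last two rows can be masked without altering a session, a visit or the treatment.

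**2. The plan's own sample size**

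Inputs from Study population and sample size: d = 0.85, independent t-test, 80% power, 5% level (sidedness not stated; two-sided assumed), 23 per group.

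Formula: power = P(|T| > t_crit), where T is noncentral t with df = 2n − 2 and noncentrality d × √(n/2).

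- n = 22: power 78.6%.
- n = 23: noncentrality 0.85 × √11.5 = 2.88, power 80.5%.

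So 23 per group (46 in total) reproduces.

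**3. What a reading shift would do (illustration only)**

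Let b be a systematic shift, in SD units, that reading adds to exercise-arm values when there is no true effect. The rejection rate follows from the same formula with b in place of d. The documents give no value for b; the range below is assumed.

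| b (SD, assumed) | Noncentrality at 23 per arm | Error rate, 23 per arm | Error rate, 30 per arm | b / 0.85 |
|---|---|---|---|---|
| 0 | 0 | 5.0% | 5.0% | 0% |
| 0.1 | 0.34 | 6.3% | 6.7% | 12% |
| 0.2 | 0.68 | 10.2% | 11.9% | 24% |
| 0.3 | 1.02 | 16.9% | 20.8% | 35% |

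The column for 30 per arm is the recruited 60 with no loss. A fixed bias does more harm in a larger sample, because the standard error shrinks and the bias does not.

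The calculation uses the single-time-point t-test that sized the trial. The Statistical analyses section plans a two-way mixed ANOVA of group and time, so these are not error rates for the planned test.

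**4. Effect of masking on the design figures**

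None. Sample size, significance level, power and visit schedule stay as they are.

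**The case against.** The strongest objection is that this turns silence into a decision. The blinding statements name participants, assessors and researchers conducting assessments; none mentions whoever later processes the recordings. This is a condensed article, and file coding may be set out in a full protocol or analysis plan that is not shown. That much stands: a reader might infer that the plan abandons all blinding, or that video readers are known to be unblinded, and the documents support neither. What remains is that the article does more than omit a detail. It declares the trial non-blinded, gives a reason that does not reach the extraction step, and lists the consequence as a limitation without the mitigation that its own recording method allows.

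Three further objections also limit the point:

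- **Mechanism.** The article does not say whether angles come from manual marking or automated tracking, nor how IMU data are processed. The room for reader judgement is therefore unknown.
- **Benefit.** A reader might infer that coding files would remove the bias. It would not. Participants are asked to "reach forward and to the side as far as possible without losing balance", which depends on effort, and they do so unblinded in front of unblinded testers. Unequal effort or encouragement is already in the recording. The EMG and evoked-potential measures are not read from video at all.
- **Staffing.** Resources are stated to be limited, and no team member unaware of allocation is identified. The person who randomises is separated only from recruitment. Excluding testers as readers is not enough, since a reader could have held the adherence conversation or supervised the first session. In a small team some recognition of participants may persist.

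**Conclusion.** The point holds in a limited form. The reason given for open assessment applies to the live session. The key primary kinematics, including the measure that sizes the trial, are extracted later from stored video, and no masking of that step is stated. One avoidable component of measurement bias is therefore left in place on the text as written.

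Its size is unknown. The 6% to 17% range at 23 per arm rests on an assumed shift of 0.1 to 0.3 SD, attributed wholly to reading and applied to a single two-sided t-test. It shows sensitivity and is not an estimate. The documents do not support a claim that the trial's error rate is inflated by any particular amount, or that masked reading would make the primary outcome free of bias. This is a low-cost improvement worth making; the article contains no error of calculation here.

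**What to change.** Keep data collection open and mask the extraction:

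1. An existing team member, for example the person who does the allocation, replaces video, IMU and EMG file names with random codes and holds the key.
2. Videos are analysed in shuffled batches without arm or visit labels and with faces masked. Where possible the reader is a team member who neither tested that participant nor delivered that participant's adherence conversation or first exercise session.
3. IMU and EMG signals are processed by scripts locked before the allocation key is released.
4. The limitation is amended to say that session conduct is unblinded, that outcome extraction is masked, and that bias from participant effort and tester encouragement remains.

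If masked reading is already arranged elsewhere, a clarifying sentence in Randomisation and in the limitations box is enough.

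Cost: file coding and batch handling, and some delay before individual results are available. No added visit is needed, and no added reader if a suitable team member can be found. Some recognition of participants may remain in a small team.
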